#### Educational program plus progressive exercise program

The control intervention consists of biomedical and surgery-specific education before surgery and an exercise manual after surgery. To control for differences in attention between the two interventions, patients in the educational program will also have two meetings before and four meetings after surgery with members of the research team (in person or through telephone).

The pre-surgical, biomedical and surgery-specific education is based on a previously developed educational intervention for spinal patients [26]. In the first preoperative in person meeting (30–45 min), a ‘not-blinded’ neurosurgeon will provide verbal information on the preparation for surgery, surgery itself and recovery from surgery, stressing the importance of postoperative exercises. Questions raised by the patient are discussed. A booklet is provided with information about the following topics: structure of the spinal column and spinal diseases; examinations before surgery; the operative environment; surgical procedures; anesthetic procedures; postoperative care and postoperative pain reduction. A second telephone meeting a second telephone meeting of 10–15 min with the same neurosurgeon is planned 1–2 weeks after to answer question about the given information and to discuss point that are unclear.

After surgery and before discharge from the hospital, a physiotherapist will meet the patient (meeting of circa 20 min) and provide him with instructions about the exercise program. Patients will receive a manual describing exercises to be performed in the weeks following surgery. The exercise program is based on the program of Abbott et al. [27] and consist of dynamic exercises to gradually enhance endurance capacity of the back and leg muscles, stretching and cardiovascular exercises. Patients keep a daily diary, for the duration of 8 weeks, tracking on paper their training activity, signing a ‘X’ every time they performed their daily muscle reinforcement exercises, stretching exercises and cardiovascular exercises. Two, five and seven weeks after discharge patients are contacted by telephone (a circa 20 min telephone meeting) by a physiotherapist. For safety reasons, patients will be asked to increase the number of repetitions as long as their pain remains tolerable. They will be asked to gradually increase the repetitions according to their perceived pain. During the telephone sessions, their training progress is discussed and patients are remembered to mark their training activity in the diary. Patients are asked to bring the diary to the 2 months follow-up visit, to check for compliance to the training instructions. The providers of the educational sessions will be trained and have to follow the manual that was created for this program, to assure that all sessions will be held in the same way. Although not exactly the same, the time points of the fourth, fifth and sixth educational session come close to the time points of the fourth, fifth and sixth session of the CBT intervention, which are at 2–5 weeks, 3–6 and 4–8 weeks post-surgery, respectively. The providers of the educational sessions will be trained and have to follow the manual that was created for this program, to assure that all sessions will be held in the same way in both sites.

All patients, independently from randomization into one of the groups, will be routinely prescribed medications for pain control and will be referred for physical therapy on an out-patient basis in different sites or an in-patient basis in specialized rehabilitation centers following lumbar spinal fusion surgery, depending on the needs.

### Outcome measures

Primary and secondary outcomes will be measured at baseline preoperatively and 2, 6 and 12 months after surgery (Table 2). Investigators and research assistants collecting outcomes from patients at different time points during follow-up will be blinded to group assignment. The psychologists delivering the CBT and the clinicians providing the educational program to the control group cannot be blinded. Nevertheless, patients will be blinded to the study hypotheses and will be informed that the study is examining the comparative benefits of two treatments that are given in addition to usual care and that may potentially improve outcomes. The patients will not be informed about the likely association between a high PCS score and lower outcomes after spinal fusion surgery, neither about the fact that the control intervention will not address catastrophizing.

**Table 2 Tab2:** Outcome measures. (Days-D, Weeks-W, Months-M)

***Outcomes***	***Instrument***	***Study Period***	***Enrollment***		***Surgery***					
		***Time***	***≥ 6 W***	***Intervention*** ***Between 4 W preop***	***Baseline***	***4D***	***Intervention*** ***Between 8 W postop***	***8 W***	***6 M***	***12 M***
*Primary outcome:*										
Self-reported function	COMI		X					X	X	X
*Secondary outcomes:*										
Self-reported Pain intensity	NRS		X			X		X	X	X
Self-reported disability	ODI		X					X	X	X
Self-reported daily-function and quality of life	EQ-5D		X					X	X	X
Self-reported mood and cognition	PROMIS depression		X					X	X	X
Patient’s global impression of change	PGIC		X					X	X	X
Self-reported pain catastrophizing	PCS		X					X	X	X
Medication Usage	MQS		X					X	X	X
Work productivity and activity impairment	WPAI:LBP		X					X	X	X
*Other variables:*										
Patient demographics	Medical record		X							
Surgical complications	Clavien-Dindo							X		
Self-reported anxiety	PROMIS anxiety		X					X	X	X
Self-reported fear of surgery	SFQ		X					X	X	X
Self-reported fear avoidance beliefs	FABQpa		X					X	X	X

#### Primary outcome

The primary outcome is the patient’s score on the COMI 12 months after surgery. The COMI is a self-administered multidimensional instrument that consists of seven items which assess the extent of the patient’s back pain and leg pain, difficulties with functioning in everyday life, symptom-specific well-being, general quality of life, and social and work disability. Leg pain and back pain are assessed on 0–10 graphic rating scales and all other items on 5-point adjective scales. In each case, a higher score indicates worse status [28]. The instrument is validated in Italian and Dutch [29, 30].

#### Secondary outcomes

Secondary outcomes are leg/back pain, disability, quality of life, depression, patient’s global impression of change, pain catastrophizing, pain medication regimen, and work productivity and activity impairment. These will be measured using the following questionnaires:
Numeric Rating Scale (NRS) for back and leg pain. Pain intensity is assessed on an 11-point scale ranging from 0 (no pain at all) to 10 (the worst imaginable pain) [31].Oswestry Disability Index (ODI): a self-administered questionnaire, assessing a patient’s limitations in activities of daily living. The ODI has ten questions scored on a 6-point scale. The total score ranges from 0 to 100, with higher scores denoting higher functional disability [32].European Quality of Life Five Dimension Five Level Scale (EQ-5D-5L): This questionnaire assesses health related quality of life in terms of five dimensions: mobility, self-care, usual activities, pain/discomfort, and anxiety/depression [33]. Each of the 5 items are scored on a 5-point scale, ranging from no problems in that domain to extremely problematic.Depression is measured by the PROMIS (Patient-Reported Outcomes Measurement Information System) Short Form v1.0 - Depression 8b [34]. The eight questions are scored from 0 to 5. Higher scores denote higher levels of depression.Patient’s Global Impression of Change (PGIC): This scale assesses patient’s own assessment improvement or deterioration over time on a 7-point scale (1. very much improved - 7. very much worse).Pain Catastrophizing Scale (PCS): The PCS is a 13-item scale that measures catastrophic thinking in relation to pain. Each item is scored on a 5-point scale ranging from 0 (never) to 4 (always) [23]. Higher scores denote higher levels of catastrophizing. Psychometric properties of the PCS have been studied extensively in a variety of patient populations having painful disorders and found to be good to excellent [35, 36]. In addition, the PCS has been shown to be sensitive to psychosocial interventions designed to increase the use of adaptive coping strategies and decrease the use of maladaptive coping strategies, such as pain catastrophizing [37].Medication Quantification Scale (MQS): The MQS is an instrument or quantifying medication regimen use in chronic pain populations. The score is calculated for each medication by taking a consensus-based detriment weight for a given pharmacologic class and multiplying it by a score for dosage. The calculated values for each medication are then summed for a total MQS score. The score can provide a useful point measure of medication usage for any pain medication regimen [38, 39].Work productivity and activity impairment will be assessed using the Work Productivity and Activity Impairment questionnaire: Low Back Pain (WPAI:LBP) [40]. This questionnaire measures the effect of the specific health problem ‘low back pain’ on work productivity and activity impairment. Specific outcomes are absenteeism (work time missed), presenteeism (impairment while working), overall work impairment (absenteeism plus presenteeism), and activity impairment (impairment in regular activities) due to LBP. Each score is represented as a percentage, and higher scores indicate less productivity or greater impairment.

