
#### Other variables of interest

The following patient characteristics will be gathered: gender, age, weight, height, civil state, employment status (e.g. retired, no paid work), type of working activity (e.g. sedentary, physical, job absent or reduced due to the pain), educational level, smoking status, allergies, low back pain duration, other chronic pain complaints, sickness benefits and length of current sick leave, self-reported psychiatric problems, and concomitant physiotherapy.

The following medical data will be gathered: type of operation, surgical indication, American Society of Anesthesiologists (ASA) classification.

Preoperative state anxiety will be assessed by the PROMIS (*Patient-Reported Outcomes Measurement Information System*) Short Form v1.0 – Anxiety 4a. The PROMIS Anxiety instruments measure self-reported fear (fearfulness, panic), anxious misery (worry, dread), hyperarousal (tension, nervousness, restlessness), and somatic symptoms related to arousal (racing heart, dizziness). Additionally, surgical fear will be measured by the ten-item Surgical Fear Questionnaire as a predictor of physical and emotional recovery [41]. Each item refers to a specific potential consequence of the operation (intervention) and is scored on an 11-point scale (from no fear to most extreme fear).

Fear avoidance belief will be assessed with the four Fear Avoidance Beliefs Questions that make up the “physical activity” part of the FABQ (denominated FABQpa) [42]. This is a patient reported questionnaire that specifically focuses on how a patient’s fear avoidance beliefs about physical activity and work may affect and contribute to their low back pain and resulting disability. Moreover, surgical complications will be recorded using the Clavien-Dindo classification system for postoperative complications of spinal fusion (therapy-oriented, 4-level severity grading) [43]. There will be no reporting of (severe) adverse events as this study is investigating the effect of a therapy (CBT therapy versus education/exercises) which does not pose a specific risk to the patients. At most patients might experience a mild emotional discomfort, but this is very seldom as these therapies are known to give benefit to patients.

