All patients randomized (i.e. those with a PCS score > 24) will be analyzed in an intention-to-treat analysis. To test for a difference between the CBT and control group in the COMI at 12 months, linear regression will be used, with correction for baseline COMI and center. In addition, the difference in the trajectory of COMI over time will be assessed by means of linear mixed-effects regression, taking all follow-up measurements into account. Adjustment for center, type of surgery, age and gender will be made and, if necessary, for other prognostic variables significantly associated with the outcome (i.e., acute postoperative pain intensity, severity of catastrophizing, preoperative depression, preoperative surgical fear, length of current sick leave, pain duration). Stepwise backward elimination using the Wald test will be used to select prognostic variables significantly associated with the outcome. Any control variables that are incomplete will be imputed if the proportion of incomplete patients exceeds 0.05. We will use multiple imputation with fully conditional specification with the number of imputations set to the percentage of incomplete patients. Predictive mean matching will be used to draw values to be imputed. Secondary outcome variables will be analyzed similar to the primary outcome. For these, logistic regression analysis adjusted for center will be used to test for differences in proportions at 12 months postoperatively.

Exploratory, we will compare the outcomes of the patients in the two intervention groups with the outcomes of patients with low pain catastrophizing scores (i.e. those with a PCS score < 24) undergoing care as usual. Linear mixed-effects regression for the three groups will be performed with primary and secondary outcomes at the three postoperative assessment periods and controlling for preoperative values. This analysis will indicate whether high catastrophizing patients follow a similar trajectory of pain and functioning after spinal fusion surgery compared non-catastrophizing patients.

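### WPAI presenteeism, and overall work impairment where it needs presenteeism, exist only for patients at work, so analysing them like COMI compares groups formed after randomisation

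*Protocol article*

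**What the plan says.** Under Secondary outcomes, the protocol article names the WPAI:LBP and its scores: "Specific outcomes are absenteeism (work time missed), presenteeism (impairment while working), overall work impairment (absenteeism plus presenteeism), and activity impairment". The last is described as "activity impairment (impairment in regular activities) due to LBP", so it is not tied to having a job. Every score is a percentage, and "higher scores indicate less productivity or greater impairment".

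Employment is not an inclusion criterion (Participants and recruitment). Other variables of interest shows that non-workers are expected: it records "employment status (e.g. retired, no paid work"), working activity with the category "job absent or reduced due to the pain", and "sickness benefits and length of current sick leave".

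Power considerations and statistical analysis places all randomised patients in an intention-to-treat analysis. It compares COMI at 12 months by linear regression corrected for baseline COMI and center, and adds a mixed model over the follow-up visits. For the rest: "Secondary outcome variables will be analyzed similar to the primary outcome". The only elaboration is logistic regression for proportions. No exception is made for WPAI. On missing data: "Any control variables that are incomplete will be imputed if the proportion of incomplete patients exceeds 0.05".

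**The concern.** A patient who is retired, without paid work or fully on sick leave has no presenteeism score. A regression of 12-month presenteeism therefore uses only patients at work at 12 months, and correction for baseline needs a score from before surgery as well.

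The trial's own rationale makes it plausible that treatment affects who is in that group. The Background calls catastrophizing a predictor of work disability, and the PCS cut-off was first taken from a whiplash study that predicted work status. If CBT lowers catastrophizing and more patients return to work, the extra returners enter the CBT mean while their control counterparts stay out of it. A higher score means worse, so a real benefit could be reported as no effect or as harm on a named secondary outcome.

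**Working it through.** **1. The plan's own figure.** The article gives no number for WPAI. Its COMI figure reproduces: difference 2, SD 2.5, so d = 2/2.5 = 0.80. With 42 per arm and two-sided alpha 0.05, t-test power is 0.952 (stated: 0.95). With 15% dropout, 42/0.85 = 49.4, so 50 per group and 150 over three groups. Nothing below changes this.

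**2. Which scores exist for whom, from the article's definitions.**

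| Score | Retired or no paid work | Employed, fully on sick leave | At work |
|---|---|---|---|
| Activity impairment | yes | yes | yes |
| Absenteeism | no | yes (can be 100%) | yes |
| Presenteeism | no | no | yes |
| Overall work impairment | no | depends on an unstated rule | yes |

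**3. Illustration of the sign (all inputs assumed).** There are 25 employed patients per arm. Control: 12 at work, mean presenteeism 30%. CBT: the same 12 improved by 5 points to 25%, plus 6 more at work at 60%. Means are not adjusted for baseline.

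- Presenteeism among those at work: CBT (12×25 + 6×60)/18 = 660/18 = 36.7%; control 30.0%. CBT looks 6.7 points worse.
- Absenteeism in all employed (at work 0%, off work 100%): CBT 7/25 = 28%; control 13/25 = 52%. Correct direction.
- Overall impairment, full absence scored 100%: CBT (300 + 360 + 700)/25 = 54.4%; control (360 + 1300)/25 = 66.4%. Correct direction. If the score is undefined off work, it follows presenteeism.

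**4. When the sign reverses.** With returners at r%, the CBT mean exceeds 30 when (300 + 6r)/18 > 30, that is r > 40. At r = 40 the means are equal, so the benefit is hidden. Below 40 CBT looks better.

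**5. What baseline correction does.** If the six returners were off work at enrolment, they have no baseline presenteeism. A complete-case regression drops them and compares 25% with 30%: the right sign, but blind to the six returns. If their baseline value is imputed, or if they were working at enrolment, they stay in, and the effect in step 3 can appear, less whatever part baseline explains.

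**6. Leaving employment.** Absenteeism goes wrong by a different route. If 5 of the 13 off-work controls leave employment and are dropped, control is 8/20 = 40%. If 2 CBT patients return and none leave, CBT is 11/25 = 44%. Keeping the leavers at 100% gives 13/25 = 52% against 44%. A rule for leavers is therefore needed.

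**7. Precision.** The employed share is not given. If 30, 40, 50, 60, 70 or 80% of 42 per arm have a work score (n = 13, 17, 21, 25, 29, 34), power at d = 0.80 is 0.50, 0.62, 0.72, 0.79, 0.85 or 0.90.

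**The case against.** The analysis rule is a one-line summary covering eight instruments, similar is not identical, and scoring rules and not-applicable coding often sit in an analysis plan. That holds for the scoring details. It does not dispose of the main point, because the article does more than leave a gap: it states a rule for all secondary outcomes, and for presenteeism that rule cannot be carried out as an intention-to-treat comparison.

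A reader might infer more than the article supports:

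- **That every work score needs presence at work, or that all can reverse on return to work.** Absenteeism needs a job, not presence, and moves the right way in step 3. Activity impairment is defined for everyone.
- **That leaving out patients not employed at enrolment biases the comparison.** That status is fixed before randomisation; the cost is precision.
- **That overall impairment can exceed 100% because it is described as a sum.** The description is a parenthetical gloss on a cited questionnaire whose scoring is not shown, so no scoring error can be claimed.
- **That the imputation rule will fill in baseline scores that do not exist.** The rule covers incomplete control variables and does not say whether not applicable counts as incomplete. This is one possible reading, worth closing off.

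It also stands that reversal needs returners clearly more impaired than existing workers, and that this concerns parts of one secondary questionnaire.

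**Conclusion.** The point holds for presenteeism, and for overall work impairment where that requires presenteeism. Followed as written, the analysis conditions on being at work after randomisation, which treatment may change, and the result can hide or reverse a return-to-work benefit. The 6.7-point reversal shows that this is possible, not how likely it is: the working shares and impairment levels are assumed, and in that example the sign turns only when returners exceed 40%. That non-workers lack these scores is inferred from the article's definitions, not stated in it. The primary COMI analysis and sample size are unaffected. This should be corrected before analysis, but it does not threaten the trial's main conclusion.

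**What to change.** In the statistical section, replace the blanket rule for WPAI with the following:

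1. WPAI activity impairment, defined for every patient, is the between-arm WPAI test, analysed like COMI.
2. Absenteeism and overall work impairment are analysed in patients employed at enrolment, a subset fixed before randomisation. Full sick leave is scored 100%, and one fixed rule, the same in both arms, covers patients who leave employment during follow-up.
3. Working status at each follow-up is reported by arm.
4. Presenteeism is presented descriptively, labelled as conditional on being at work.
5. Baseline work scores that are not applicable are not imputed.

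WPAI and baseline employment status are already collected. The rule for leavers requires that a change of employment can be identified at follow-up, which should be confirmed. The cost is that presenteeism loses its formal test and the work scores rest on fewer patients, by an amount the article does not allow one to fix.

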
#### Other variables of interest

The following patient characteristics will be gathered: gender, age, weight, height, civil state, employment status (e.g. retired, no paid work), type of working activity (e.g. sedentary, physical, job absent or reduced due to the pain), educational level, smoking status, allergies, low back pain duration, other chronic pain complaints, sickness benefits and length of current sick leave, self-reported psychiatric problems, and concomitant physiotherapy.

The following medical data will be gathered: type of operation, surgical indication, American Society of Anesthesiologists (ASA) classification.

Preoperative state anxiety will be assessed by the PROMIS (*Patient-Reported Outcomes Measurement Information System*) Short Form v1.0 – Anxiety 4a. The PROMIS Anxiety instruments measure self-reported fear (fearfulness, panic), anxious misery (worry, dread), hyperarousal (tension, nervousness, restlessness), and somatic symptoms related to arousal (racing heart, dizziness). Additionally, surgical fear will be measured by the ten-item Surgical Fear Questionnaire as a predictor of physical and emotional recovery [41]. Each item refers to a specific potential consequence of the operation (intervention) and is scored on an 11-point scale (from no fear to most extreme fear).

Fear avoidance belief will be assessed with the four Fear Avoidance Beliefs Questions that make up the “physical activity” part of the FABQ (denominated FABQpa) [42]. This is a patient reported questionnaire that specifically focuses on how a patient’s fear avoidance beliefs about physical activity and work may affect and contribute to their low back pain and resulting disability. Moreover, surgical complications will be recorded using the Clavien-Dindo classification system for postoperative complications of spinal fusion (therapy-oriented, 4-level severity grading) [43]. There will be no reporting of (severe) adverse events as this study is investigating the effect of a therapy (CBT therapy versus education/exercises) which does not pose a specific risk to the patients. At most patients might experience a mild emotional discomfort, but this is very seldom as these therapies are known to give benefit to patients.

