Furthermore, this study can demonstrate efficacy of the CBT intervention for high catastrophizing patients, but it does not assess cost-effectiveness. Although some cost elements are included (medication use, further treatment, employment status), no full cost analyses will be conducted. Moreover, if this study shows a positive effect on pain and disability from perioperative CBT, this will not clarify the optimal dosage of the intervention or the ideal timing. Finally, it cannot clarify whether a PCS score of 24 or higher is the most optimal cut-off for offering patients CBT. Future studies should conduct sensitivity analyses to establish at which level of pain catastrophizing intervention should be offered, to come to an optimal cost-benefit ratio.

In conclusion, the results of this study are expected to provide valuable information that will potentially change clinical practice of lumbar spinal fusion surgery. If our study can demonstrate that perioperative CBT is effective in improving clinical outcome after lumbar spine fusion surgery in high catastrophizing patients, it is highly recommended to perform prescreening to identify this subgroup for which a perioperative psychological treatment will be indicated. If CBT will not prove to be superior and if this study will confirm that high levels of pain catastrophizing have a negative impact on clinical outcome, that might be a reason to be very reluctant in offering these patients a spinal fusion procedure, trying to opt for less invasive treatment options.

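### Adverse event reporting is expressly excluded, complications are scheduled only at 8 weeks, and neither reoperation nor the promised further-treatment data has a place in the schedule up to the 12-month endpoint

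*Protocol article*

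**What the plan says.** All references are to the protocol article.

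- **Adverse events.** Under Other variables of interest: "There will be no reporting of (severe) adverse events as this study is investigating the effect of a therapy". The ground given is that the study concerns a therapy "which does not pose a specific risk to the patients"; the worst effect foreseen is mild emotional discomfort.
- **Complications.** The same section says that "surgical complications will be recorded using the Clavien-Dindo classification system for postoperative complications of spinal fusion". In Table 2 (Outcome measures) the row "Surgical complications", instrument "Clavien-Dindo", has a single mark, in the 8-week column. Its 6-month and 12-month cells are empty. The row stands under other variables, not among the secondary outcomes.
- **Safety wording in the control arm.** Under Educational program plus progressive exercise program: "For safety reasons, patients will be asked to increase the number of repetitions as long as their pain remains tolerable".
- **Further treatment.** The Discussion says that some cost elements are included and lists them as "medication use, further treatment, employment status". Neither Table 2 nor the sections on secondary outcomes and other variables gives further treatment an instrument or a time point.
- **Reoperation.** No section provides for recording it.
- **Endpoint.** The primary outcome is COMI at 12 months after surgery.

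**The concern.** A trial in patients having spinal fusion would be expected to keep a simple record of serious events in both arms, even when the randomized components are thought benign. Here the article does not merely leave the matter to a fuller document. It states a rule that such events are not reported, and an analysis plan cannot tabulate what the protocol says is not reported.

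The stated reason is also incomplete. Emotional discomfort is a possible effect of the psychological program. The other arm receives a manual of exercises that patients increase themselves after surgery, and the article puts a safety limit on that increase. The absence of risk is therefore assumed in one section and qualified in another.

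Two things are at stake. The first is safety information: a serious event, reoperation or implant-related complication after week 8 has no place in the described data. The second is interpretation. Reoperation or additional treatment before month 12 can change a patient's COMI score, and a reader of the 12-month result would want to know how often it happened in each arm.

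**Working it through.** **1. The plan's own sample size, which fixes the numbers per arm.** Inputs from Power considerations and statistical analysis: difference 2, SD 2.5, power 0.95, type-I error 0.05 (sidedness not stated; two-sided assumed), dropout 15%.
- d = 2 / 2.5 = 0.80.
- A two-sample t-test needs 41.6, so 42 per arm; power at 42 is 0.952.
- 42 / 0.85 = 49.4, so 50 per group; 3 × 50 = 150.

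The stated 42 per group and 150 in total are reproduced.

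**2. What is scheduled, and when.**

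| Item | 8 weeks | 6 months | 12 months |
|---|---|---|---|
| COMI | yes | yes | yes |
| NRS pain, ODI, PROMIS depression, PGIC, MQS | yes | yes | yes |
| Surgical complications | yes | no | no |
| Adverse events | excluded in the text | excluded | excluded |
| Reoperation | no provision | no provision | no provision |
| Further treatment | said to be included; no row | no row | no row |

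Concomitant physiotherapy is listed among patient characteristics. The only Table 2 row that seems to hold these is the demographics row, marked at enrollment alone.

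**3. How much follow-up the 8-week mark covers.** 8 / 52 = 15% of the year. This share needs context. The last CBT session falls at 4–8 weeks after surgery. The control diary runs for 8 weeks, and the last telephone call is 7 weeks after discharge. The mark therefore falls at about the end of both programs. What it misses is the period from then to the endpoint, 44 of 52 weeks.

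**4. How many events could be missed.** The documents give no rate, so this is an assumed range. With 50 enrolled per arm and 2% to 10% of patients having an event after week 8: 50 × 0.02 = 1 and 50 × 0.10 = 5 patients per arm.

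**5. What a record could and could not show.** If no event is seen in an arm, the one-sided 95% upper limit for its rate is 1 − 0.05^(1/n): 6.9% for n = 42 and 5.8% for n = 50.

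For a two-sided comparison of two proportions at 0.05 with n per arm and mean proportion p̄, power = Φ{[|p1 − p2| − 1.96 √(2p̄(1 − p̄)/n)] / √[(p1(1 − p1) + p2(1 − p2))/n]}. With n = 42 and assumed rates:
- 5% vs 10%: 14%
- 5% vs 15%: 33%
- 5% vs 20%: 55%

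A harms table would inform, but a test on it would not. The record should be descriptive.

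**The case against.** Several stronger readings are tempting, and the document does not support them.

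- *That harms are never compared between arms.* Back and leg pain, disability, depression, PGIC and MQS are secondary outcomes measured to 12 months, and the analysis section treats secondary outcomes like the primary one. Lasting deterioration, including pain provoked by exercise, would show there, and MQS compares pain medication directly. But these measures record status. They do not say that a patient was reoperated, had an implant problem or suffered a serious event.
- *That harm from the programs themselves would go unseen.* The 8-week mark falls at about the end of both programs, so complications arising during delivery have a place in the schedule.
- *That physical rehabilitation, and so its risk, belongs to one arm.* All patients are referred for physical therapy whatever their allocation; only the manual-based program is specific to the control arm. The safety sentence is a precaution, in tension with the no-risk statement but no proof of a hazard.
- *That further treatment is not collected.* The Discussion says it is included. The missing row shows a mismatch within the article, and the form itself may sit in a fuller document.
- *That complications are not compared.* The article states no comparison, but an analysis plan that is not shown could tabulate the 8-week data.
- *That the COMI result cannot be attributed to CBT.* The primary analysis is by intention to treat. Reoperation after randomization may itself be a consequence of allocation, so leaving it unrecorded does not bias the randomized contrast.

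These objections narrow the point. They leave standing the express exclusion, the single 8-week mark, the absence of any provision for reoperation, and the unmatched statement on further treatment.

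**Conclusion.** The point holds in a limited form. It rests on one explicit rule (no adverse event reporting), one schedule entry (complications at 8 weeks only), one absence (reoperation up to 12 months) and two mismatches within the article (further treatment; risk of the programs). The exclusion is in the prose; the schedule itself shows only the single mark.

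The primary inference is intact. The loss is in safety information and in reading the 12-month result. Its size cannot be taken from the document; 1 to 5 patients per arm follows only from the assumed 2% to 10%. This is a low-cost improvement that should be made, not a flaw that threatens the main comparison.

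**What to change.** 1. In Other variables of interest, replace the exclusion sentence with, for example: Serious adverse events, surgical complications (Clavien-Dindo) and reoperations will be recorded in all groups at the 8-week, 6-month and 12-month contacts and tabulated descriptively by group.
2. In Table 2, add the matching marks at 8 weeks, 6 months and 12 months, and a further-treatment row with its source and time points, so that the table agrees with the Discussion.
3. Reconcile the no-specific-risk statement with the safety wording on exercise progression. This concerns consistency of the text; no change to the exercise rule is proposed here.
4. Report the number of reoperated patients by arm beside the COMI result. Do not exclude or adjust for them, since that would condition on an event after randomization.

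Cost: a few form items at contacts already held, one descriptive table and a minor amendment. No formal tests of harms should be promised, as they would be underpowered at this size. Events in patients already past a contact would have to be sought from medical records.
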